## Interim analysis

Interim analyses will be programmed during the study. Interim analysis of data collected is programmed upon completion of follow-up of the first 15 and 30 patients to eventually discontinue the study in the case of excess adverse events or mortality.

In case of excess serious expected adverse drug reactions, deaths or SUSARs the Data Monitoring Committee will evaluate the results of the analysis in order to decide whether triiodothyronine treatment has provided proof “beyond reasonable doubt” that for all or for some specific type of patients, the trial treatment is clearly contraindicated in term of net difference in mortality and/or adverse drug reactions. Appropriate criteria of “proof beyond responsible doubt” cannot be specified precisely, but in general, a difference of at least 3 standard deviations in *ad interim* analysis of mortality and/or adverse drug reactions would be needed to justify halting or modifying the trial prematurely. In this case, the sponsor will discontinue the study and provide an analytical report to the competent authority within 4 weeks. During interim analysis, the Data Monitoring Committee is obliged to evaluate whether enrolled patients meet the inclusion and exclusion criteria according to the protocol, whether the protocol is being followed, the acceptability of data being accrued, the success of planned accrual targets and the appropriateness of the design assumptions.

Data Monitoring Committee is composed of the representative of the sponsor, Professor of Anaesthesiology [name], Professor of Pharmacology [name], Assistant Professor of Pharmacology [name] and Director and Cardiologist [name].

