**7 WITHDRAWAL OF PATIENTS AND DEVIATION FROM THE PROTOCOL**

**Specification on criteria for withdrawal of patients: Patient and Investigator criteria**

Clinical follow-up will be performed for all patients randomized in the study even when they are withdrawn for any reason. If for any patient either the study treatment or observations were discontinued the reason will be recorded and documented in the CRF. Withdrawn subjects will be replaced and after the end of the study the number and reasons of withdrawn subjects will be reported both in treatment and placebo group.

Reason that a patient may discontinue participation in this clinical study are considered to constitute one of the following:

- Subject or relative withdrew informed consent
- Unsatisfactory adherence to study protocol or protocol violation (including drug dosage administered, and visit attendance)
- Appearance of clinical status that render the patient unsuitable to continue the study
- Adverse effects related to drug/placebo administration
- Major (cardiac and non-cardiac death, cardiac arrest, reinfarction) and minor (potentially life-threatening arrhythmias) adverse events during the period of drug/placebo administration
- Necessity of therapy with drugs interfering with T3 such as amiodarone or anti-thyroid drugs.

Analysis of data collected programmed upon completion of follow-up of the first 30 patients to eventually discontinue the study in the case of excess adverse events or mortality. In the case of occurrence of a major event, drug/placebo administration will be promptly stopped.

The subject may withdraw from the study at any time without explanation, without losing the right to future medical care. The participation of the subject may, at any moment, be terminated by the investigator, if considered appropriate.

**Any deviation from the protocol (to be classified as Major and Minor) will be accepted only in case of emergency and/or after agreement with the Sponsor.**

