## Known Drug reactions

### Oral Anticoagulants: T3 appears to increase catabolism of vitamin K-dependent clotting factors. If oral anticoagulants are also being given, compensatory increases in clotting factor synthesis are impaired. It is likely that a reduction in anticoagulant dosage may be required.

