### Adverse drug reaction (ADR)

A response to a medicinal product which is noxious and unintended [DIR 2001/83/EC Art 1(11)]1. Response in this context means that a causal relationship between a medicinal product and an adverse event is at least a reasonable possibility (see Annex IV, ICH-E2A Guideline).

Adverse reactions may arise from use of the product within or outside the terms of the marketing authorisation or from occupational exposure [DIR 2001/83/EC Art 101(1)]. Conditions of use outside the marketing authorisation include off-label use, overdose, misuse, abuse and medication errors.

(All AEs judged by either the reporting investigator or the sponsor as having a reasonable causal relationship to a drug).

1. The relationship between an AE and a drug is considered **Certain** when:

The AE occurs in a plausible time relation to the administration of the drug and cannot be explained by a concurrent disease or other drugs or chemicals. The response to withdrawal of the drug (dechallenge) should be clinically plausible. The event must be definitive pharmacologically or phenomenologically, using a satisfactory rechallenge procedure if necessary.

1. The relationship between an AE and a drug is considered **Probable** when:

The AE occurs in a reasonable time relation to the administration of the drug, it is unlikely to be attributed to a concurrent disease or other drugs or chemicals and it follows a clinically reasonable response on withdrawal (dechallenge). Rechallenge information (AE reappearance after drug reintroduction) is not required to fulfill this definition.

1. The relationship between an AE and a drug is considered **Possible** when:

The AE occurs in a reasonable time relation to the administration of the drug, but it could also be explained by a concurrent disease or other drugs or chemicals. Information on drug withdrawal (dechallenge) may be lacking or unclear.

- The relationship between an AE and a drug is considered **Unlikely** when:

a causal relationship cannot be definitively ruled out, but

- other drugs, chemicals or underlying disease provide plausible explanations

and/or

- the temporal relation to the administration of the drug makes a causal relation improbable.

**An AE is considered Not Related** to a drug in case of:

- existence of a clear alternative explanation, and/or

- unreasonable temporal relationship between Drug and Event, and/or

- non plausibility.

**An AE is considered Unassessable** when:

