### Reporting Duties of the Investigator

The Investigator must report any Serious AE (whether or not thought to be related to the investigational drug) by faxing the CRF-AE recording pages **no later than 24 hours** after knowledge of the event to:

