### Reporting Duties of Uni-Pharma

Uni-Pharma shall ensure that all relevant information about any Serious and Unexpected Adverse Events considered at least “Possible related” to triiodothyronine (SUSARs) will be reported to the Competent Authorities and Ethics Committees (following general and local rules and procedures), with these deadlines after the knowledge:

- fatal and life threatening unexpected cases, no later than 7 days;
- other unexpected serious cases, no later than 15 days.

Uni-Pharma shall ensure that all information and supporting documentation that subsequently become available, will be also reported as soon as possible to the Competent Authorities.

Since this study is blinded, the patient’s treatment code should be broken (procedure to be specified) before the reporting to the Competent Authorities and the Ethics Committees.

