## Criteria for the termination of the trial

Data Monitoring Committee will terminate the study before completion and provide an analytical report to the competent authority of each concerned Member State within 4 weeks in case of excess deterioration is recorded in response to treatment, such as deaths, excess serious expected adverse drug reactions, or SUSARs.

Under normal circumstances, the end of the trial will be the date of the last visit of the last patient participating in the trial.

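### The interim safety looks are aimed at all adverse events, but the stated comparison between arms covers only deaths and reactions judged to be drug-related, so unattributed non-fatal harms, most clearly bleeding, can fall outside it

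*Protocol*

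**What the plan says.** Protocol section 14, Interim analysis, places looks after follow-up of the first 15 and the first 30 patients. It gives their purpose in the words that section 7 also uses for the 30-patient look: "to eventually discontinue the study in the case of excess adverse events or mortality".

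The sentences that follow make this operational in three steps:
- The committee's evaluation is triggered by an excess of deaths, serious expected adverse drug reactions (ADRs) or SUSARs.
- The committee then decides whether "the trial treatment is clearly contraindicated in term of net difference in mortality and/or adverse drug reactions".
- A difference of at least 3 standard deviations in mortality and/or ADRs is offered as a general guide to stopping.

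Section 12 separates the terms. An adverse event needs no causal link to treatment. ADRs are glossed as "All AEs judged by either the reporting investigator or the sponsor as having a reasonable causal relationship to a drug". The grade Unlikely is available where "other drugs, chemicals or underlying disease provide plausible explanations". The sponsor's reporting duties define a SUSAR as at least possibly related to T3.

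Criteria for the termination of the trial (section 14) has the committee end the study "in case of excess deterioration is recorded in response to treatment, such as deaths, excess serious expected adverse drug reactions, or SUSARs".

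**The concern.** The purpose is stated in terms of adverse events, whatever their cause. The trigger, the comparison and the guide are stated in terms of deaths and events that have passed a causality judgement. This is not detail left for a statistical analysis plan: the Protocol has itself fixed the compared quantity, and fixed it more narrowly than the purpose given in the same section.

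The point matters because the expected background is heavy. Expected Serious Adverse Events (section 12) lists most events of interest as expected in ventilated COVID-19 patients. Blinded, case-by-case attribution cannot be relied on to remove only the background events. A comparison by randomised arm needs no attribution.

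**Working it through.** **1. Which events can fall outside.** The categories in the Interim analysis text, set against section 12:

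| Category named | Needs a causality judgement? |
|---|---|
| Deaths | No |
| Serious expected ADRs | Yes |
| SUSARs | Yes, at least possible |
| Other non-fatal adverse events | Not named |

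Bleeding is the clearest exposed event. It is in Expected Serious Adverse Events and absent from Expected adverse drug reactions. Known Drug reactions (section 9) nevertheless says, under oral anticoagulants, that "T3 appears to increase catabolism of vitamin K-dependent clotting factors", and says that T3 can affect the action of heparin.

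**2. The plan's own figures.** The Protocol gives no operating characteristics for the 3-SD guide, so there is none to reproduce. Its power statement (84% for 15% against 50%, 30 per arm) reproduces at 84.3% and is unaffected.

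**3. What 3 SD requires at the 30-patient look.** With 15 per arm, z = [(x_T − x_P)/15] / √[2p̄(1 − p̄)/15], where p̄ = (x_T + x_P)/30.

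- 9 vs 1: 0.5333 / √(2 × 0.3333 × 0.6667/15) = 0.5333/0.1721 = 3.10.
- 8 vs 0 (one background event removed from each arm): 0.5333/0.1615 = 3.30.
- 6 vs 0 (two drug-caused events also left unattributed): 0.4000/0.1461 = 2.74.

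The smallest T3 counts that reach 3 SD are 7 against 0, 9 against 1 and 11 against 2.

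**4. Chance of reaching 3 SD.** Exact binomial enumeration, 15 per arm. Counted placebo rate = b × background; counted T3 rate = b × background + d × excess. Here b and d are the shares of background and drug-caused events attributed to the drug. Assumed: background 10%, excess 40 points (true rates 10% vs 50%).

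| d | b | P(z ≥ 3) |
|---|---|---|
| 1 | 1 (all events counted) | 26.6% |
| 1 | 0 (only background removed) | 39.0% |
| 0.75 | 0 to 1 | 13.1% to 11.6% |
| 0.5 | 0 to 1 | 1.8% to 3.2% |

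With b = 0 no placebo event is counted, so the entry is simply P(X ≥ 7) for X binomial with n = 15: rate 0.40 gives 39.0%, 0.30 gives 13.1% and 0.20 gives 1.8%.

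Break-even: if attribution removed every background event, it would still do worse than counting everything once fewer than 89% of drug-caused events were attributed. The figure is 82% at 20% vs 60% and 80% at 30% vs 70%.

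**5. Smaller excesses and the first look.** Counting every event, 10% vs 30% reaches 3 SD with probability 3.2%. The ThyRepair rates in section 9 give 0.4% for atrial fibrillation (7.7% vs 19%) and 0.2% for minor haemorrhage (12% vs 19%). At the 15-patient look (split 7/8), even 10% vs 50% gives only 1.8% to 3.0%. In this range the 3-SD bar decides the outcome, and the choice of counted events hardly matters.

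**The case against.** Several parts of the Protocol soften the gap.

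- Section 8 gives the committee unblinded data and lets it oversee the frequency of expected events. Section 12 has every serious adverse event reported whatever its relatedness. The termination list is open, being introduced as examples, and the 3-SD figure applies only in general.
- Section 3 records major and minor events, bleeding included, with no causality filter, and section 14 plans tests on them.
- Section 7 stops study drug for any patient with a major event.
- The route to Unlikely is narrow. Possible also allows for a concurrent-disease explanation, serious events are judged as though the patient were on active drug, and attribution by either the investigator or the sponsor is enough.
- Heparin is to be adjusted to aPTT, and the Protocol reports no serious haemorrhage in ThyRepair.

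Much of this stands. A reader might infer that non-fatal harms would escape monitoring. The documents do not support that, because the committee may see these events and may act on them. A reader might also take arrhythmia, infarction and hypotension as equally exposed. They are weak examples, since section 12 lists all three as T3 reactions. Nor does attribution always weaken detection: a filter that removed only background would raise the chance from 27% to 39%.

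What does not stand is that any of these passages supplies the missing comparison. Section 8 is permissive and sets none. The section 14 tests on recorded events are not tied to the looks. The termination text is confined to deterioration in response to treatment, and its examples repeat the same three categories. Stopping drug in one patient is not a comparison of arms.

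**Conclusion.** The point holds as a mismatch inside the current text: the stated between-arm comparison is narrower than the stated purpose of the looks, and non-fatal events that nobody attributes to T3 can fall outside it. This conclusion rests on the wording alone.

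The practical size is modest. The effect on formally reaching 3 SD is material only when the true excess is large and some drug-caused events go unattributed: in the example, 27% falls to 12-13% with three quarters attributed and to 2-3% with half. The event rates (10% vs 50%) and the attributed shares are assumptions; the Protocol gives neither. At the ThyRepair rates the change would almost never move the formal guide. Its value there is that the committee's stated table would include the events the looks were set up to watch. This is a cheap improvement, not evidence that harms would be missed.

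**What to change.** In section 14, Interim analysis, keep the mortality and ADR comparisons and add a comparison by randomised arm, regardless of attribution, of:
- all serious adverse events; and
- the T3-linked events already listed in section 5.5, by type: atrial fibrillation, flutter or paroxysmal supraventricular tachycardia; ventricular fibrillation or sustained ventricular tachycardia; new myocardial infarction; cardiogenic shock and hypotension; bleeding.

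Add the same events to the examples in Criteria for the termination of the trial. The ADR comparison should stay as a comparison and not become a listing, because good attribution improves detection.

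The cost is a wording amendment; the data are already collected under sections 5.5, 5.6, 11 and 12, and the committee exists. The downsides are more comparisons at each look, sparse counts by type (about 7 vs 0 or 9 vs 1 is needed for 3 SD at 15 per arm), and more background events in the table. Background dilutes a combined count: the same 40-point excess gives 17% at 30% vs 70%, against 27% at 10% vs 50%, which is the reason to compare by type. These are acceptable because the 3-SD figure guides committee judgement and is not a fixed boundary.

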## Criteria for the termination of the trial

Data Monitoring Committee will terminate the study before completion and provide an analytical report to the competent authority of each concerned Member State within 4 weeks in case of excess deterioration is recorded in response to treatment, such as deaths, excess serious expected adverse drug reactions, or SUSARs.

Under normal circumstances, the end of the trial will be the date of the last visit of the last patient participating in the trial.

## Procedure to account for missing or spurious data

All efforts will be directed towards minimizing the amount of missing data likely to occur. The percentage of missing values for a given variable in this study is expected not to exceed 5%.

Imputation of missing data is going to be performed based upon maximum-likelihood methodology. The maximum-likelihood based strategies fit a model by an iterative process (the Expectation maximisation algorithm). Multiple imputation methods generate multiple copies of the original dataset replacing missing values by randomly generated values and analyse them as complete sets.

Mixed effects models are proposed to be used to impute missing data of repeated measurements over time outcomes. Time of measurement may be considered as a random variable and these models may estimate a slope to summarize each patient’s response.

A sensitivity analysis will be performed at the end of the study in order to justify the choice of the particular method applied for handling missing data. Sensitivity analysis will consist of the following steps:

1. Comparison of the results of two analyses, one assigning the best possible outcome to all missing values in both groups and the other assigning the worst possible outcome to all missing values in both groups
2. Comparison of the results of two analyses, one assigning the best possible outcome to missing values in the control group and the worst possible to those of the experimental group and vice-versa.
3. Comparison of the results of the full set analysis to those of the complete case analysis

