**14. STATISTICAL ISSUES**

Specification on statistical evaluation for efficacy and safety parameters

Continuous variables will be described using descriptive analysis like mean and median value, standard deviation, range, minimum and maximum; categorical variables will be described using relative and absolute frequencies.

Summary values will be expressed as mean ± SD. Categorical data will be compared by using Chi-square and the Fisher’s exact test. Normal distribution of variables will be estimated with Kolmogorov-Smirnov test. Normally distributed data will be compared using an independent t test. Skewed data will be analyzed non-parametrically (Mann-Whitney U or Kruskal-Wallis test). Serial measurements will be compared by repeated measures analysis of variance (RMANOVA). When significant, differences within and between each group will be tested by a post hoc analysis using the Bonferroni correction for multiple comparisons. A computerized statistical program (SPSS for Windows) will be used for all analyses. All tests will be 2-sided. The p values <0.05 will be considered statistically significant.

Survival analysis will be performed using clinical data obtained at follow-up (major and minor events). Kaplan-Meier method will be used to describe the overall survival and the length of the progression-free interval. Log-rank test will be used to compare survival curves. Univariate and multivariate analysis using the Cox regression model will be performed in order to eliminate eventually confounding factors.

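### Serial outcomes: the mixed model only fills gaps before RMANOVA, and no step carries the imputation uncertainty into the test (low severity at the expected 5% missing)

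*Protocol*

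**What the plan says.** The Protocol's section 14 (Statistical issues) sets the test for repeated outcomes: "Serial measurements will be compared by repeated measures analysis of variance (RMANOVA"), with Bonferroni-corrected post hoc comparisons when it is significant.

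The subsection on missing or spurious data then sets out the handling of gaps:

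- In general: "Imputation of missing data is going to be performed based upon maximum-likelihood methodology". The next sentence explains this: "The maximum-likelihood based strategies fit a model by an iterative process (the Expectation maximisation algorithm").
- On multiple imputation: "Multiple imputation methods generate multiple copies of the original dataset replacing missing values by randomly generated values and analyse them as complete sets". This says what such methods do. No number of copies and no rule for combining results is given.
- For serial outcomes: "Mixed effects models are proposed to be used to impute missing data of repeated measurements over time outcomes". On the content of that model: "Time of measurement may be considered as a random variable and these models may estimate a slope to summarize each patient’s response". Treatment arm is neither included nor excluded.
- On the amount: "The percentage of missing values for a given variable in this study is expected not to exceed 5" per cent.
- The sensitivity steps are best and worst case for both groups, crossed extremes, and "Comparison of the results of the full set analysis to those of the complete case analysis".

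**The concern.** Read together, the two places describe a sequence: fit a likelihood model, use it to complete the table, then test the completed table by RMANOVA. A value predicted by EM or by a mixed model is a conditional mean. It has no residual scatter, and it borrows from the same patients who supply the observed data. If it is entered once, RMANOVA counts it as a full independent measurement.

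Two errors can follow. With arm in the fit, the filled values sit on their own arm's fitted profile. Within-arm scatter is then too small and the group-by-time test rejects too often. With arm left out, the filled values are drawn toward a common profile and the arm difference shrinks.

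At stake are the serial secondary outcomes: haemodynamics, pO2/FiO2, inflammatory indices and echocardiography. The mixed model that the plan already fits can test the arm difference on the incomplete data, so the detour through RMANOVA gains nothing.

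**Working it through.** **The plan's own figures.** The protocol gives no power or error figure for serial outcomes. Its one power figure, 84% for weaning at 15% v 50% with 30 per arm, reproduces: z = (0.35 − 1.96·√(2·0.325·0.675/30)) / √(0.15·0.85/30 + 0.50·0.50/30) = 1.007, so power is 84.3%. It is a binary comparison and this point does not touch it. The figure that matters here is the expected ceiling of 5% missing.

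**Inputs.** From the protocol: 30 per arm, two-sided 0.05, at most 5% missing. Assumed, because the protocol gives none: number of visits, covariance, drop-out pattern and effect size.

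**Check 1, by formula.** Take 5 visits with SD 1 and correlation 0.6 between any two. Let a fraction f of last-visit values be missing at random, with the other four observed.

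- Share of last-visit variance explained by the other four: R² = 4·0.6²/(1 + 3·0.6) = 1.44/2.8 = 0.514. A filled value therefore has variance 0.514 instead of 1.
- Variance the test sees, per patient: 1 − f·(1 − R²).
- Variance that applies with arm in the fit, approximately: R² + (1 − R²)/(1 − f).
- Ratio of reported to true SE: the square root of the first over the second. False-positive rate: 2·(1 − Φ(1.96·ratio)).

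| f | seen | true | SE ratio | false-positive rate |
|---|---|---|---|---|
| 5% | 0.976 | 1.026 | 0.975 | 5.6% |
| 20% | 0.903 | 1.121 | 0.897 | 7.9% |
| 40% | 0.806 | 1.324 | 0.780 | 12.6% |

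**Check 2, simulation of the same setting.** Covariance as in check 1; EM conditional means entered once; scattered gaps or drop-out; 1000 null runs and 400 runs with a true effect of 0.8 SD. At 5%, 20% and 40% missing, the last-visit SE ratio was 0.95-0.99, 0.88-0.89 and 0.75-0.78. The last-visit false-positive rate was 5-6%, 8-9% and 12-14%. Both agree with the formula. The group-by-time test is hit harder, because every filled visit contributes:

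| Missing | Group-by-time false positives, arm in fit | Last-visit estimate of a true 0.80, arm left out |
|---|---|---|
| 5% | 5.5-7% | 0.79-0.81 |
| 20% | 13-18% | 0.75-0.77 |
| 40% | 25-45% | 0.74-0.77 |

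At 40% the shrinkage is 1 − 0.767/0.80 = 4% to 1 − 0.736/0.80 = 8%. With arm left out, the group-by-time false-positive rate stayed near nominal (about 5-6% at 20-40% missing).

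**Check 3, simulation with patient slopes.** 8 visits; random intercept SD 1, slope SD 0.8, residual SD 0.7; monotone drop-out from visit 3; an effect that grows over time to 0.80 at the last visit; mixed-model fill-in. There were two runs, with 250-400 null replicates and 150 effect replicates each.

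- Arm in the fit, no effect: 4-6% on complete data; 4% and 7% at about 5% missing; 11% and 13% at 23-24%; 24% at 38% and 35% at 41%.
- Arm left out: the estimate was 0.73 at 5% missing, 0.58 at 24%, 0.38 at 38% and 0.36 at 41%.
- Mixed model used directly as the analysis: 4% false positives at 23% missing and 9% at 38%, with a large-sample test. Small-sample degrees of freedom were not tried.

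**Simulation error.** Around a true 5%, 1.96·√(0.05·0.95/n) is 2.7 points for n = 250, 2.1 for n = 400 and 1.4 for n = 1000. At 5% missing, the 4-7% range is hardly distinguishable from complete data.

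**The case against.** The strongest reply is that noise-free single fill-in is an inference. A reader might take the plan to say that fitted values are analysed as though observed. It does not. The same subsection describes several copies with randomly generated values, and with arm in the model and proper pooling that would be valid. The wording is also permissive: mixed models are proposed, and the sensitivity paragraph leaves room for choosing the method. All this stands. What remains is that multiple imputation is not assigned to serial outcomes, the method named for them is mixed-model imputation, and RMANOVA is the stated test.

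Model terms, number of copies and pooling are commonly left to a SAP. That stands too, and their absence is not the point here. The point is a stated choice: a model that could be the analysis is used only as a gap-filler.

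A reader might also infer that the treatment effect will be roughly halved (0.80 to 0.38), or that false positives could reach 37% or 72%. The documents do not support either. The halving needs arm left out, which the protocol does not say, 38% missing, and an effect carried by slopes. Under compound symmetry the shrinkage at 40% missing was 4-8%. The 37% and 72% came from EM fitted separately by arm at 22% and 38% missing, which estimates an eight-visit covariance from 30 patients; the protocol does not make that choice.

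Is more than 5% missing likely? Daily measurements and 48-hourly echocardiography are scheduled only during ICU stay (section 11), while follow-up runs to 30 days. An RMANOVA extended past ICU discharge would need many filled values. But those days are unscheduled, and the protocol does not say that they would be analysed. So 20% or more in living patients is possible but not shown.

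The planned sensitivity steps would help to expose a result that hangs on filled values. None of them carries imputation uncertainty into the RMANOVA.

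**Conclusion.** The point holds as a low-severity weakness in a stated method. The likelihood model is given an imputation role only, RMANOVA is the test, and nothing stated passes imputation uncertainty from one to the other.

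If values are filled once, the direction of both errors is established. Their size depends on the missing fraction: negligible to small at the protocol's 5%, and material from about 20%. The false-positive rates rest on assumed covariance and random drop-out. The amount of shrinkage depends so strongly on the assumed model that no single figure should be quoted.

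Only secondary serial outcomes are affected. How values absent after death are treated is a separate question.

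**What to change.** For serial outcomes, replace imputation followed by RMANOVA with a mixed model fitted directly to the observed values. Include arm, visit as a category, arm-by-visit, baseline value, a within-patient covariance structure and small-sample degrees of freedom, and report arm differences at named days.

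Alternatively, state that multiple imputation is used for these outcomes, with arm in the imputation model and results pooled by Rubin's rules.

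Keep the sensitivity steps already listed.

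The cost is a change of wording. SPSS, the package that the protocol names, fits mixed models, and no extra patients or measurements are needed. The downside is that some nominally significant secondary results may disappear.
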